| Trial monitoring           | 501-505, 521-524, 542-545 | Frequency and procedures for monitoring trial conduct. If there is no monitoring, give explanation                                                                                                                                                                                                                                                                                                                                                                                                                                                                                                                                                                                                                                                                                                                                                                                                                                                                                                                                                                       | 21,22        |
| Ethics              |                           |                                                                                                                                                                                                                                                                                                                                                                                                                                                                                                                                                                                                                                                                                                                                                                                                                                                                                                                                                                                                                                                                          |              |
| Research ethics approval   | 501-505                   | The ethical clearance (Appendix 11) with protocol reference number WSU HREC 023/2025 was approved by the Walter Sisulu University, Faculty of Medicine and Health Sciences Ethics and Biosafety Committee. Access approval (Appendix 12) was obtained from the Eastern Cape Provincial Health Research Committee (reference number EC_202503_022).                                                                                                                                                                                                                                                                                                                                                                                                                                                                                                                                                                                                                                                                                                                       | 21           |
| Protocol amendments        | 501-505

542-545    | Any substantive protocol modifications will be submitted for prior review and approval by the Walter Sisulu University, Faculty of Medicine and Health Sciences Ethics and Biosafety Committee and the Eastern Cape Provincial Health Research Committee before implementation. Approved amendments will be documented with version control and communicated to all relevant study personnel and sites. Participants will be informed of any changes that may influence their participation or consent.                                                                                                                                                                                                                                                                                                                                                                                                                                                                                                                                                                  | 21,22        |

|                               |                    |                                                                                                                                                                                                                                                                                                                                                                                                                                                                                                                                                                                                                    |       |
|-------------------------------|--------------------|--------------------------------------------------------------------------------------------------------------------------------------------------------------------------------------------------------------------------------------------------------------------------------------------------------------------------------------------------------------------------------------------------------------------------------------------------------------------------------------------------------------------------------------------------------------------------------------------------------------------|-------|
| Consent or assent             | 506-507            | The research staff at each site will be responsible for obtaining voluntary informed consent form.                                                                                                                                                                                                                                                                                                                                                                                                                                                                                                                 | 21    |
|                               |                    | N/A                                                                                                                                                                                                                                                                                                                                                                                                                                                                                                                                                                                                                | 16    |
| Confidentiality               | 510-518            | To maintain confidentiality, all questionnaires and other study documents will have an identification number. Research records will be kept in a locked filing system until the completion of the study at WSU, and all electronic information will be securely stored in a password-protected computer and backed up to a password-encrypted storage cloud with two-factor authentication access. The data will be available and provided to the research team, including the principal investigator, research assistants, supervisors, and the biostatistician, for the purposes of analysis and report writing. | 21    |
| Ancillary and post-trial care | 364 -365 & 529-530 | Provisions, if any, for ancillary and post-trial care, and for compensation to those who suffer harm from trial participation                                                                                                                                                                                                                                                                                                                                                                                                                                                                                      | 15,22 |

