|                                   |         | Package for Social Sciences), software version 29. The study will employ descriptive analyses of intervention participants' responses, utilizing means, standard deviations, medians, and interquartile ranges, as appropriate, based on the distribution's normality. Outcome measures of participants in the intervention group will be compared with those in the control group using an appropriate t-test, chi-squared test, Wilcoxon sum-ranked test, and/or the Fisher's exact test, depending on the normality of the distribution, and or the value of the expected frequencies. The study will compare pre- and post-interview guide summative scores using the paired t-test or the Wilcoxon signed-rank tests to ascertain patients' mental health status and quality of life (comparing post-test with pre-test scores) and whether mental health status and quality of life have changed after four months (comparing follow-up post-test with pre-test scores). Univariable and multivariable analyses will also be undertaken using logistic regression to determine the effectiveness of health promoters on the primary outcome measures and factors that are associated with mental health risk among cervical cancer survivors. The risk ratio (RR) will be the relative measure of association used. The 95% confidence interval (95% CI) will be used to assess the precision of estimates at the 5% level of significance ( $p \leq 0.05$ ). |    |

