|                             | 255-269

364-367 | 
The control group will continue to receive the usual care for cervical cancer treatment. At the end of the intervention period, the participants with cervical cancer in the control group will be revisited for outcome measures. They will further be referred to health facilities for definitive diagnosis and management of their mental health if at risk.
 
Referral pathways to psychiatric or crisis services are in place for those mental health patients who are excluded, ensuring they are not left without support. Notwithstanding, patients living with cervical cancer who have suicidal ideation may benefit from integrated mental health services, and their exclusion could delay access to care
    | 10, 15 |
| Outcomes                    | 242-245                | Primary outcomes: quality of life, and mental health indicators (anxiety and depression scores - GAD-7 and PHQ-9) will be evaluated in both groups as primary outcomes.                                                                                                                                                                                                                                                                                                                                                                                                                                                                                                                                                               | 9      |
|                             | 244-245                | Secondary outcomes will include attendance rate, retention, and data completeness at intervention sessions.                                                                                                                                                                                                                                                                                                                                                                                                                                                                                                                                                                                                                           |        |

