|                                             |         | will be monitored through emotional check-ins, supervision meetings, and participant reports. All concerns will be documented, reviewed, and addressed following ethical guidelines for participant safety.                                                                                                                                                                                                                                                                                                                                                                                                                                        |       |
| Participant timeline                        | 252-255 | In the intervention group, four interventions will be implemented at one-month intervals, each followed by an evaluation of quality of life and mental health status outcomes. The four evaluations in the intervention group will run concurrently with those in the control group.                                                                                                                                                                                                                                                                                                                                                               | 10    |
| Sample size                                 | 286-299 | $n = \frac{(\sigma_1^2 + \sigma_2^2)(Z_{1-\alpha} + Z_{1-\beta})^2}{(\mu_1 - \mu_2)^2}$ 
The sample size was calculated using the equation, for a two-sided 95% confidence interval, where <math>\alpha = 0.05</math>, <math>Z_{1-\alpha} = 1.96</math>, and for 80% power, <math>Z_{1-\beta} = 0.84</math>. The mean difference <math>\mu_1 - \mu_2 = 1</math> and the standard deviation (<math>\sigma</math>) = 2. The sample size was calculated using a two-sample means formula, assuming a mean difference of 1 and a standard deviation of 2, which corresponds to a medium standardized effect size (Cohen's <math>d = 0.5</math>).
 | 12-13 |

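### The planned logistic regression yields odds ratios, not the risk ratio named as the effect measure, and its effectiveness analysis needs dichotomised scores although the trial was sized on means

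*Protocol*

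**What the plan says.** The analysis text stands in the row on the protocol and statistical analysis plan of the SPIRIT checklist and is repeated under Statistical methods.

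- **Between-group tests.** The arms are first compared "using an appropriate t-test, chi-squared test, Wilcoxon sum-ranked test, and/or the Fisher's exact test, depending on the normality of the distribution".
- **Regression.** Next: "Univariable and multivariable analyses will also be undertaken using logistic regression to determine the effectiveness of health promoters on the primary outcome measures". The same sentence extends the model to factors associated with mental health risk.
- **Effect measure.** The sentence after that reads: "The risk ratio (RR) will be the relative measure of association used". Neither place names a log-binomial or Poisson model, or a way to derive a risk ratio from the logistic fit.
- **Endpoints.** The Outcomes row lists quality of life and "mental health indicators (anxiety and depression scores - GAD-7 and PHQ-9) will be evaluated in both groups as primary outcomes". It gives no binary version and no cut-off.
- **Sizing.** The Sample size row states: "The sample size was calculated using a two-sample means formula, assuming a mean difference of 1 and a standard deviation of 2". The calculation is described as "for a two-sided 95% confidence interval" with 80% power. The rows on randomisation and allocation concealment give 128 participants, 64 per arm.

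**The concern.** Two things do not fit together.

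First, the named model and the named measure differ. An analyst who follows both sentences literally fits a logistic model and then has an odds ratio where the text calls for a risk ratio. If that number is labelled a risk ratio, every non-null association lies further from 1 than it should. The distortion grows with the frequency of the outcome. It would reach both the treatment effect and the associated-factors analysis.

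Second, this regression is assigned to determine effectiveness on outcomes that are scores. Binary logistic regression, the form that goes with a risk ratio, can be fitted to them only after each score is cut in two. The sample size gives 80% power for a difference in means and makes no allowance for the information lost by a cut. The regression is also the only multivariable analysis described, so as written the only adjusted estimate of effect would be a dichotomised one.

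**Working it through.** **1. The plan's own sample size.** Inputs from the Sample size row: difference 1, SD 2 in each arm, Z values 1.96 and 0.84.

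n per arm = (σ₁² + σ₂²)(1.96 + 0.84)² / (difference)² = (4 + 4) × 7.84 / 1 = 62.72, so 63 per arm. The t-distribution version gives 63.77, so 64 per arm and 128 in total, as stated. Power at 64 per arm is 80.1% (t) to 80.7% (normal approximation). The stated size is therefore right for a comparison of means.

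**2. Odds ratio against risk ratio.** With control risk p₀ and intervention risk p₁:

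RR = p₁/p₀ and OR = [p₁/(1 − p₁)] / [p₀/(1 − p₀)].

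The protocol gives no event rates, so all of these are assumed.

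| Control risk | Intervention risk | RR | OR |
|---|---|---|---|
| 50% | 30% | 0.60 | 0.43 |
| 40% | 20% | 0.50 | 0.375 |
| 20% | 10% | 0.50 | 0.44 |
| 50% | 35% | 0.70 | 0.54 |
| 10% | 7% | 0.70 | 0.68 |
| 10% | 8% | 0.80 | 0.78 |

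In the second row OR = (0.20/0.80)/(0.40/0.60) = 0.25/0.667 = 0.375. A 50% reduction in risk would read as about 62%. In the last two rows the two measures nearly agree.

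**3. Power of the dichotomised analysis.** Take the plan's standardised difference, d = 1/2 = 0.5, and assume normal scores with a higher score meaning worse. For a cut-off that puts a proportion p₀ of controls at risk,

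p₁ = 1 − Φ(z + 0.5), where z is the standard normal value exceeded with probability p₀.

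Power by the arcsine approximation is Φ(h√(64/2) − 1.96), with h = 2·arcsin√p₀ − 2·arcsin√p₁. A two-proportion z calculation is shown beside it, with the number per arm that it requires for 80% power.

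| Assumed p₀ | p₁ | Power, arcsine | Power, z | n per arm for 80% |
|---|---|---|---|---|
| 20% | 9.0% | 44% | 42% | 160 |
| 30% | 15.3% | 52% | 51% | 126 |
| 40% | 22.6% | 57% | 57% | 110 |
| 50% | 30.9% | 60% | 60% | 102 |

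At p₀ = 20%, for example, h = 0.318, h√32 = 1.80, and Φ(1.80 − 1.96) = 0.44. Outside this range, power is about 29% to 30% at a control risk of 10% and peaks at about 61% near 60%. No assumed cut-off comes close to 80%.

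**The case against.** Four points can be made for the plan.

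- **The scores are also compared without dichotomising.** The t-test or Wilcoxon comparison comes first and the regression is an addition. This stands. A reader might infer that the trial as a whole loses much of its 80% power. The document does not support that: nothing says that the logistic model replaces the comparison of scores or is the primary analysis. The power figures above belong to the added analysis only.
- **An odds ratio misleads only if it is read as a risk ratio.** This also stands. A reader might infer that the report will exaggerate the benefit and every association. The text does not say that exponentiated coefficients will be labelled risk ratios. Null associations are unaffected, and in the unadjusted two-arm comparison an odds ratio of 1 and a risk ratio of 1 are the same hypothesis. Risk ratios could also come from simple two-by-two tables or from standardised risks after a logistic fit. But the protocol states no such route, so the mismatch remains.
- **A binary analysis is reasonable in itself.** The questionnaires are used for screening, control participants found at risk are referred, and chi-squared and Fisher's exact tests are listed. Fair: an at-risk analysis beside the scores is not an error. It is a poor vehicle for the only adjusted estimate of effect on outcomes sized as means.
- **Details may sit in a separate analysis plan.** Cut-offs may well be left there. The contradiction between model and measure is in the protocol's own consecutive sentences, and such a plan would have to add or override something to resolve it.

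**Conclusion.** Wrong as written, and it should be fixed before analysis. The stated model does not produce the stated measure, and this conclusion rests on no assumption.

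The size of the consequence does rest on assumptions. If the output is called a risk ratio, the overstatement is material for common outcomes with sizeable effects (0.375 in place of 0.50 at 40% versus 20%). It is slight when the outcome is rare, and the absolute gap shrinks as the effect approaches none. The 44% to 60% power applies to the logistic effectiveness analysis alone, under normal scores, d = 0.5, 64 per arm and control risks of 20% to 50%.

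The sample size and the planned t-test or Wilcoxon comparison are not called into question by this point.

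**What to change.** 1. **Scores.** For the adjusted effect on quality of life, PHQ-9 and GAD-7, replace logistic regression by a linear model adjusted for the baseline score. Report the mean difference with its 95% confidence interval. This matches the sizing.
2. **Binary mental health risk.** State the cut-off, then choose one of two routes. Either obtain the risk ratio from Poisson regression with log link and robust standard errors, from a log-binomial model, or from standardised risks after the logistic fit. Or keep logistic regression, report odds ratios under that name and delete the risk ratio sentence.
3. **Covariates.** Do not put hospital in a model alongside arm yet. The Sequence generation row describes randomising at hospital level, while the Allocation concealment row has participants randomly assigned to two groups of 64. If the two hospitals are the randomised units, arm and hospital coincide and their effects cannot be separated. These rows must be reconciled first.

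The cost is a few sentences in the two places where the analysis text appears. No further data or participants are needed, and the models are generalised linear models available in the named software.

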| Intervention and comparator | 252-255 & 440-443      | In the intervention group, four interventions will be implemented at one-month intervals, each followed by an evaluation of quality of life and mental health status outcomes. The four evaluations in the intervention group will run concurrently with those in the control group. The intervention will be implemented by trained Health promoters utilising the Motivational Interviewing Training New Trainers Manual, along with a pocket guide for motivational interviewing and a participant's manual on substance abuse, during the intervention.                                                                                                                                                                           | 10,19  |
|                             | N/A                    | Criteria for discontinuing or modifying allocated intervention/comparator for a trial participant (e.g., drug dose change in response to harms, participant request, or improving/worsening disease)                                                                                                                                                                                                                                                                                                                                                                                                                                                                                                                                  | N/A    |
|                             | 447-551                | To enhance adherence to the mental wellness intervention, participants will receive regular SMS and phone call reminders before each health promoter-led session to support adherence. Attendance will be tracked, with follow-ups conducted within a week for those who miss sessions. Health promoters will offer motivational counselling and brief check-ins, while session logs will record engagement and barriers to ensure the intervention is delivered as intended.                                                                                                                                                                                                                                                         | 19     |

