|----------------------------|---------------------------|--------------------------------------------------------------------------------------------------------------------------------------------------------------------------------------------------------------------------------------------------------------------------------------------------------------------------------------------------------------------------------------------------------------------------------------------------------------------------------------------------------------------------------------------------------------------------------------------------------------------------------------------------------------------------------------------------------------------------------------------------------------------------------------------------------------------------------------------------------------------------------------------------------------------------------------------------------------------------------------------------------------------------------------------------------------------------|--------------|
|                            |                           | be the relative measure of association used. The 95% confidence interval (95% CI) will be used to assess the precision of estimates at the 5% level of significance ( $p \leq 0.05$ ).                                                                                                                                                                                                                                                                                                                                                                                                                                                                                                                                                                                                                                                                                                                                                                                                                                                                                   |              |

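### Three unranked primary outcomes share an unadjusted 5% level with no success rule or primary time point, so the single-comparison design of 5% error and 80% power is not delivered

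*Protocol*

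**What the plan says.** All references are to rows of the protocol's SPIRIT 2025 checklist.

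- **Outcomes:** "quality of life, and mental health indicators (anxiety and depression scores - GAD-7 and PHQ-9) will be evaluated in both groups as primary outcomes". There is no order among the three and no statement of how many must be positive.
- **Intervention and comparator; Participant timeline:** "four interventions will be implemented at one-month intervals, each followed by an evaluation of quality of life and mental health status outcomes", and "The four evaluations in the intervention group will run concurrently with those in the control group". The comparator text mentions only one control assessment: "At the end of the intervention period, the participants with cervical cancer in the control group will be revisited for outcome measures".
- **Statistical methods** (same text under Protocol and statistical analysis plan): the arms are compared by t-test, Wilcoxon, chi-squared or Fisher's exact test, as the data require. "The 95% confidence interval (95% CI) will be used to assess the precision of estimates at the 5% level of significance", with p ≤ 0.05. No adjustment or testing order is given. Four months is mentioned only for the paired pre-post comparison.
- **Sample size:** "The sample size was calculated using the equation, for a two-sided 95% confidence interval", with 80% power, a mean difference of 1 and a standard deviation of 2. The calculation is not tied to any of the three outcomes.
- **Allocation concealment mechanism:** 64 participants per group.

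**The concern.** A 5% level and 80% power describe one test. With three outcomes of equal standing, they describe the trial only if a rule says how the three results combine into one conclusion. The protocol gives the level and the power but not the rule.

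At stake is the meaning of a positive result. If the investigators see one of three scores cross p = 0.05 and report the intervention as effective, the error behind that claim is not 5%. If they decide that all three must cross, the trial is less likely to succeed than its stated power suggests. A choice made after the results are known protects neither figure. The unnamed time point adds a further choice.

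**Working it through.** **Inputs from the protocol.** Three primary outcomes; two-sided α = 0.05 (z = 1.96); 80% power (z = 0.84); difference 1; SD 2, so d = 0.5; 64 per arm. **Assumed, because the protocol gives none:** correlations between outcomes, between evaluations, and between baseline and follow-up.

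**1. The protocol's own figure.** n per arm = (σ₁² + σ₂²)(1.96 + 0.84)² / (difference)² = (4 + 4)(2.80)² / 1 = 62.72, so 63. Solving with the t distribution gives 63.77, so 64. The planned 64 per arm is correct for one comparison, with power 80.1% (t) or 80.7% (normal).

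**2. Any one of three counts, one time point.** If independent: 1 − 0.95³ = 0.143. Under correlation, from simulated trivariate normal test statistics:

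| Assumed correlation between outcomes | Chance of at least one false positive |
|---|---|
| 0 | 14.3% |
| 0.3 | 13.6% |
| 0.5 | 12.5% |
| 0.7 | 10.9% |
| 0.9 | 8.4% |

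**3. All three must succeed, one time point.** The false-positive rate cannot exceed 5%. With d = 0.5 on every outcome, simulated power is about 62% at correlation 0.5 and about 73% at 0.9. Independence would give 0.807³ = 0.526. Power reaches the single-test figure only if the outcomes are perfectly correlated.

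**4. Worst reading: between-group tests at all four evaluations.** That is 3 × 4 = 12 tests. The simulated chance of at least one false positive runs from about 38% (outcome correlation 0.3, visit correlation 0.5) to about 18% (0.8 and 0.9). The schedule allows this reading, but the protocol does not state it.

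**5. Cost of control at one time point.** The strictest Holm step uses α = 0.05/3 = 0.0167. With 64 per arm and d = 0.5, power for a given outcome at that step is 65.6% by t-test. A baseline-adjusted analysis with baseline correlation r acts on d/√(1 − r²):

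- r = 0.3: 0.5/√0.91 = 0.524, power 70%.
- r = 0.5: 0.5/√0.75 = 0.577, power 79.8%.

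To keep 80% power at α = 0.0167 with the t-test would take 86 per arm, 172 in total.

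**The case against.** **Testing at every visit.** A reader might infer that twelve between-group tests are planned, each at 5%. The protocol does not say so: "four interventions will be implemented at one-month intervals, each followed by an evaluation" schedules assessments, not tests. The analysis text compares post-test with pre-test, the Data management row speaks of baseline and post-intervention assessments, and the comparator text has controls revisited at the end of the period. These point to one post-intervention comparison. This part of the objection stands, so the 18–38% range is only a worst reading. What remains is that no primary time point is named for the between-group test.

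**Success on any one outcome.** A reader might also infer that one positive outcome is enough. That rests on silence, since no rule is stated either way. The point survives because the all-three rule fails on power instead.

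**Unseen statistical analysis plan.** A multiplicity procedure commonly sits there, and the document at hand is a checklist of excerpts, so an adjustment may exist elsewhere. But the point does not rest on a missing procedure. The protocol itself fixes three equal primary outcomes, a flat 5% level and a single-comparison sample size, and these do not fit together. An adjustment made later would leave the stated 80% power wrong.

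**Pilot.** The Patient and public involvement row calls the Phase II intervention a pilot, which softens a strictly confirmatory reading. The Background and Statistical methods rows nevertheless speak of determining effectiveness.

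**Conclusion.** The point holds in a limited form. The stated 5% and 80% do not both apply to a conclusion drawn from three unranked primary outcomes. At one post-intervention time point, the protocol implies either a false-positive chance of about 8–14% (any one suffices) or power of about 62–73% (all three required, at assumed correlations of 0.5–0.9). The sample size arithmetic itself is correct for a single comparison.

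The direction of both effects is certain. Their exact size is not, because the protocol gives no correlations. All figures also assume that individuals were randomised. The Sequence generation row instead describes randomisation by hospital, while the Allocation concealment row assigns participants to two groups of 64. That contradiction must be reconciled separately; under hospital-level allocation none of these error rates or powers would apply.

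**What to change.** Name the evaluation after the fourth session as the confirmatory time point for the between-group comparison, and reconcile the two descriptions of when controls are assessed. Then choose one of:

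- **(a)** Test quality of life, PHQ-9 and GAD-7 at that time point with Holm's procedure at an overall two-sided 5%.
- **(b)** Name one primary outcome, tie the assumed difference and SD to it, and make the other two secondary.

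Under either option, report the earlier months as estimates with confidence intervals.

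**Cost.** Neither option needs new patients or new data, but the choice should be fixed before any outcome comparison is seen. Option (a) gives up power: 66% at the strictest step with the planned t-test. A baseline-adjusted analysis would raise this to about 70% or 80% (assumed baseline correlation 0.3 or 0.5), but the protocol does not plan that for the between-group test, so it would be a further change. The stated power should be restated to match. Option (b) keeps 80% power with 128 participants, at the price of giving two of the three scores secondary status.
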